## Abstract

**Background:**

Metabolic dysfunction associated steatotic liver disease (MASLD) is the most common chronic liver disorder in the world. Most patients with MASLD are undiagnosed, untreated and unreferred. Treatment depends on diagnosis and accurate staging of fibrosis risk, and therefore screening at the primary care setting coupled with consistent, timely, evidence-based, widely accessible, and testable management processes is critical. Randomized controlled trials of methods for screening, diagnosis, severity stratification, and referral are lacking. We previously validated the MASLD clinical care pathway (MCCP), a multistep algorithmic process geared to support primary care settings in screening, diagnosis, risk stratification, and suggested referral and treatment of patients with MASLD. We will evaluate the effectiveness of the MCCP intervention compared to usual care in improving MASLD care process and patient outcomes.

**Methods:**

A two-arm, parallel, cluster-randomized trial will assess the effect of the MCCP intervention comprised of an e-trigger and structured provider education on screening, diagnosis, referral, and treatment for MASLD. Clusters are Veterans Affairs (VA) patient-centered primary care clinics, called Patient Aligned Care Teams (PACTs). This 4-year study will include three phases: (1) formative assessment to explore barriers to feasibility and acceptability of intervention among providers and patients and adapt MCCP for utilization by VA PACTs, (2) cluster-randomized trial to examine the effectiveness of the MCCP compared to usual care, and (3) summative evaluation to identify patient and provider characteristics associated with effectiveness of MCCP and plan for future implementation. The primary outcome will be a composite dichotomous variable for making a new MASLD diagnosis and completing severity risk stratification of MASLD. Secondary outcomes include referral and receipt of hepatology specialty care for patients with MASLD and advanced fibrosis.

**Discussion:**

Our randomized controlled trial will be the first to systematically implement the MCCP using strategies that are clinically relevant, adaptable and scalable. If successful, the MCCP will improve outcomes for patients with MASLD through early detection, accurate risk stratification, and timely treatment within primary care settings.

**Trial registration:**

This trial has been registered on clinicaltrails.gov (# NCT06671886), registration date: 10–31-2024.

**Supplementary Information:**

The online version contains supplementary material available at 10.1186/s12913-025-12737-2.

## Introduction

Metabolic dysfunction associated steatotic liver disease (MASLD), formerly known as nonalcoholic fatty liver disease (NAFLD), is characterized by an accumulation of excess fat in the liver consequent to metabolic syndrome and has become the most common chronic liver disease in the world [1–3]. In the United States, MASLD affects 25–40% of the general adult population [4–8]. Most people with MASLD have mild or non-progressive disease [7]. However, in approximately 30% of cases, MASLD progresses from quiescent simple steatosis to a necroinflammatory disease (metabolic dysfunction associated steatohepatitis (MASH) associated with progressive hepatic fibrosis [9, 10], which may lead to cirrhosis in a substantial proportion of patients [11]. Patients with advanced hepatic fibrosis are at greatest risk of developing complications of chronic liver disease, including hepatocellular carcinoma (HCC), increased risk of cardiovascular disease and overall increase in mortality [12, 13], and are therefore the most important subgroup to identify and most urgent to treat.

High-risk groups for MALSD and advanced fibrosis can be identified in clinical practice. Most patients with MASLD (> 90%) have one or more metabolic conditions (e.g., diabetes mellitus (DM), obesity, hypertension) that are also associated with a 2–threefold increased risk of advanced hepatic fibrosis. Screening guidelines focus on people with these features. Validated noninvasive scores incorporating commonly available demographic and clinical variables (e.g., FIB- 4) as well as ultrasound-based vibration controlled transient elastography (e.g., Fibroscan) are also widely available for MASLD risk stratification. Accurate identification and risk stratification of people with MASLD are likely to have positive consequences. For all patients with MASLD, practice guidelines (e.g., American Association for the Study of Liver Disease, European Association for the Study of the Liver) recommend weight loss in overweight or obese patients as well as education about nutritional strategies, regular physical activity, and avoiding excess alcohol intake. There is compelling evidence of short and intermediate benefits of weight loss on objective-relevant outcomes. For example, a dose–response relationship was found between weight loss and resolution of MASH in a meta-analysis of 43 studies, including 2809 individuals treated with structured weight loss programs, pharmacotherapy, or bariatric surgery [14]. For patients with MASLD and advanced fibrosis, referral to a hepatology service is recommended to monitor and manage cirrhosis and HCC, use specific medications or enroll in clinical trials. At present, there is one FDA-approved pharmacologic agent for treating MASH (resmetirom) [15], and several incretins have shown highly promising results in phase 2 trials [16].

Because MASLD is largely asymptomatic and treatment depends on accurate staging of fibrosis risk, most patients with MASLD in clinical practice are undetected, unmanaged, and unreferred [17, 18]. For example, we previously conducted a structured medical record review of 251 Veterans with MASLD and found that approximately 40% had documentation of abnormal ALT, only 21.5% had MASLD mentioned as a possible diagnosis, less than 15% were counseled regarding diet and exercise, and only 10.4% were referred to a specialist [17].

Screening at the primary care setting coupled with consistent, timely, evidence-based, widely accessible, and testable management processes is critical. However, there is no evidence-based guidance on optimal methods for screening, diagnosis, severity stratification, and referral. Several groups and professional societies [3, 19, 20] advocate the use of screeners combined with clinical care pathways. However, the effectiveness of the available guidelines has not been tested in a randomized controlled study.

We previously developed and validated an electronic (e-trigger) tool [7] aimed at the identification and risk stratification of patients at high risk for moderate to advanced fibrosis in primary care in the department of Veterans Affairs (VA) [7]. In this trial, we will test the effectiveness of an intervention that adapts this e-trigger as part of a clinical care pathway for use in VA primary care. This intervention could prevent MASLD-related complications, but prospective effectiveness data are required before wide implementation is recommended. The multicomponent MASLD clinical care pathway (MCCP) study will also provide key information about the determinants of feasibility, acceptability and implementation of multicomponent clinical care pathway intervention to improve MASLD diagnosis and management in primary care**.**

## Methods

### Study design

A two-arm, parallel, cluster-randomized trial will assess the effect of a MCCP intervention comprised of an e-trigger and structured provider education on the MASLD screening, diagnosis, referral, and treatment. Clusters are VA patient-centered primary care clinics, called Patient Aligned Care Teams (PACTs). The trial will randomize 16 PACTs in a 1:1 allocation ratio to two arms: MCCP intervention versus usual care. These 16 PACTs will be randomly selected from the 37 eligible PACTs, excluding those participated in focus groups. We will also conduct mixed-methods formative and summative evaluations of the intervention throughout the 4 years of the study. The study is designed with pragmatic features to foster efficient implementation of findings into clinical care settings. Figure 1 depicts the study design and procedures.

**Fig. 1 Fig1:**
[figure not shown]
Study design

### Specific aims and hypotheses

The MCCP study is designed to test the hypothesis that the PACTs randomized to a multicomponent MCCP intervention will have increased guideline-concordant diagnosis, referral and treatment than the control PACTs. *Specific Aim 1* (formative assessment), which will be performed in year 1, is to assess barriers to feasibility and acceptability of the MCPP intervention among providers and patients and adapt MCCP for utilization by VA PACTs. *Specific Aim 2* (cluster-randomized trial), performed over years 2–4, is to examine the effectiveness of the MCCP compared to usual care in improving MASLD care process and patient outcomes. *Specific Aim 3* (summative evaluation)*,* performed in year 4, is to identify patient and provider characteristics associated with effectiveness of MCCP and plan for future implementation.

### Study setting

The study will take place at the Michael E. DeBakey VA Medical Center (MEDVAMC) in Houston, Texas, which provides care for more than 111,000 Veterans and has a total of 37 PACTs. The typical PACT core team consists of a primary care provider (physician, nurse practitioner, or physician assistant), a nurse care manager (registered nurse), a clinical associate (practice nurse or health technician), and a clerk. Teams work closely with multidisciplinary professionals including pharmacists, social workers, nutritionists, and specialist providers. The study and principal investigators will be introduced to the PACT’s lead primary care providers (PCP) during department meetings. Those who are interested will be recruited to advise on the feasibility and acceptability of the intervention.

Specialized PACTs such as infectious disease, spinal cord injury, homeless, and geriatrics are excluded due to patients facing more pressing issues. The Post-deployment PACT is excluded due to unique care needs and having only one team. We also exclude PACTs with fewer than 100 patients expected in the three-month period. Additionally, unstable PACT leadership (e.g., pending departure or vacancy) at the time of randomization will be excluded. The biostatistician will randomize PACTs into the intervention or usual care groups with a computer-generated randomization.

### Participants in specific aim 1

To understand the feasibility and acceptability of the e-trigger, the research team will identify a random sample of patients with already diagnosed MASLD and receiving care at MEDVAMC within the past year using electronic health record search and chart review. Phone call visits are excluded as they are typically brief, addressing lab results or medication changes. Potential participants will be contacted during a clinic encounter to determine interest in participating. Patients who agree to participate will be scheduled for a telephone/video interview. We will recruit patients on a rolling basis until we reach our sample goal of 20 patients or reach saturation in the themes patients are reporting. Six PACTs will be interviewed to understand the barriers and facilitators to implementing the e-trigger.

### Conceptual framework

Our multicomponent intervention design is grounded in the SELFIE (Sustainable intEgrated care modeLs for multi-morbidity: delivery, Financing and perfromanceE) Framework (Fig. 2) [21]. Care components cover the World Health Organization’s six dimensions of health systems: information, workforce, technologies, leadership, service delivery, and financing. Our interprofessional team developed the MCCP clinician education based upon consensus informed guidelines and individual risk prediction models (*Information*). The MCCP includes an interprofessional team of a provider and a nurse, at minimum, embedded within each PACT (*Workforce*). E-triggers, developed based on the Safer Dx Trigger Tool Framework [22], are used along with other clinician facing technologies such as note templates (*Technology*). Clinicians and their patients share responsibility for guiding individualized care planning that is tailored to a patient’s needs *(Leadership).* The MCCP provides recommendations on referral and treatment for MASLD patients to reduce gaps in care and proactively deliver patient-centered care (*Service delivery*). *Financing* (e.g., evaluation of cost-effectiveness) will be addressed in future studies after the MCCP effectiveness is established.

**Fig. 2 Fig2:**
[figure not shown]
Conceptual model

### Study phases and timeline

The study will be conducted in two phases over 4 years. The focus group questions will be aligned with the Consolidated Framework for Implementation Research (CFIR) 2.0 domains and constructs [23]. The second phase (years 2–4) is a cluster-randomized trial and summative evaluation of intervention effectiveness based on the Reach, Effectiveness, Adoption, Implementation and Maintenance (RE-AIM) measures to inform future implementation [24].

### Intervention

Our validated MCCP [7] includes algorithmic guidance geared towards primary care providers for the screening, diagnosis, risk stratification, referral and treatment for patients with MASLD (Fig. 3). This multistep pathway entails identification of patients at risk (Step 1), targeted history and lab testing (Step 2), noninvasive testing for hepatic fibrosis using FIB- 4 (Step 3), elective additional testing with Fibroscan for those with indeterminate FIB- 4 (Step 4), and recommended management and follow-up.

**Fig. 3 Fig3:**
[figure not shown]
MASLD clinical care pathway

Our MASLD intervention is multicomponent. First, we will identify high-risk patients using the e-trigger algorithm that was previously developed and validated among randomly selected patients in primary care at MEDVAMC aimed at the identification of MASLD and initial risk stratification of patients in VA primary care [7]. Second, we will educate and train PACT personnel on how to deal with e-trigger positive patients as well as make treatment recommendations within an interprofessional team. The e-trigger is a logistic regression model that contains three predictive variables (BMI, FIB- 4, and diabetes) with variable cut-offs defined by Youden's index, the model predicting any hepatic fibrosis (Fibroscan LSM > 7 kPa) had an area under the curve (AUC) of 0.75 (95% CI 0.67–0.84), negative predictive value (NPV) of 91.5% and positive predictive values (PPV) of 40.0%. The equation includes three predictor variables: DM (yes/no), BMI (> 33 vs. ≤ 33), and FIB- 4 (> 1 vs. ≤ 1).

We will apply our e-trigger [7] on updated data extracted from the electronic health records, which include demographics, diabetes mellitus (DM) status, body mass index (BMI), alanine transaminase (ALT), aspartame aminotransferase (AST), and platelet count (PLT) levels within the past 12 months. FIB- 4 will be calculated based on ALT, AST, PLT, and age (at time of laboratory test completion) using the formula [FIB- 4 = age (years) × AST (U/L)/[platelet counts (10^9^/L) × sqrt(ALT) (U/L)]. DM presence is defined as having at least one DM-related prescription filled and dispensed within the last year.

Patients who have all three conditions above (DM + high BMI [> 33] + high FIB- 4 [> 1]) are considered as e-trigger positive patients. Lists of e-trigger positive patients with their e-trigger data will be made available to the PACT leads and/or nurse who will perform the rest of the steps after receiving the study’s education and training.

To ensure that patients are active and have the opportunity to meet with their provider regarding their health condition, we will generate e-trigger data for patients scheduled for a visit within the next three months. Phone call visits will be excluded as they are typically brief and primarily address lab results or medication changes.

The education component of our intervention will last 2–3 weeks and will include structured and mostly didactic information on MASLD diagnosis and management, the e-trigger, and referring/managing patients through the MCCP. Training will be based on adult learning theory principles in an interactive presentation led by the study team that will include a power point presentation, role play, structured discussion and open discussion (Fig. 4).

**Fig. 4 Fig4:**
[figure not shown]
MASLD intervention

### Usual care PACTs

We will provide PACT members in the usual care study arm with published MASLD practice guidelines [7] and MASLD patient education material (identical to that provided to the MCCP PACTs) but without the e-trigger information or the detailed educational and training component. Patients in the usual care arm will receive standard of care for diagnosis and management of MASLD.

### Outcomes

Patient-level clinical outcomes will be measured at six and 12 months following the delivery of the e-trigger results to the PACT. The primary outcome will be a composite dichotomous variable of making a new MASLD diagnosis and completing severity risk stratification of MASLD. Secondary outcomes include referral and receipt of hepatology specialty care for patients with MASLD and advanced fibrosis.

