#### Mixed-methods approach for summative evaluation

Based on the RE-AIM framework, we will use a mixed-methods approach with qualitative and quantitative data to summatively evaluate the MCCP (Table 2). For example, *reach* will be assessed quantitatively by comparing patient characteristics for patients who are referred to weight loss (i.e., exercise program, endocrine clinic, medications, endoscopic or surgical bariatric procedures) and/or hepatology within a given intervention PACT and those who are not within the same PACT. For *implementation*, we will use descriptive statistics to examine the average degree of fidelity to the intervention at the PACT level. We will also examine the association between the degree of fidelity and each binary outcome at 6 and 12 months.

**Table 2 Tab2:** RE-AIM elements and corresponding measures

RE-AIM Element	Corresponding Measure
Reach: *proportion and representativeness of individuals who participate in an intervention*	1) Characteristics of MASLD patients who are referred to weight loss in a given PACT compared with characteristics of all MASLD patients in a given PACT* 2) Characteristics of MASLD patients who are referred to hepatology in a given PACT compared with characteristics of all MASLD patients in a given PACT* 3) Differences between the intervention and control groups in the relationship between patient characteristics and each primary and secondary outcome at 6 months (see Effectiveness)
Effectiveness: *impact of an intervention on important outcomes*	1) Differences in the proportions of patients with MASLD diagnosis and risk stratification between intervention and control groups* 2) Differences in the proportions of patients with MASLD who are referred to a weight loss program within 6 months between intervention and control groups * 3) Differences in the proportions of patients with advanced MASLD who are referred to hepatology within 6 months between intervention and control groups* 4) Differences in the proportion of patients with MASLD who are referred to a weight loss program and start the program within 6 months between intervention and control groups* 5) Differences in the proportion of patients with advanced MASLD referred to hepatology and are seen in a hepatology clinic within 6 months between intervention and control groups*

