Adoption: *proportion and representativeness of individuals who deliver the intervention*	1) Characteristics of PACTs participating in the study (make up of clinicians, number of clinicians in PACT) and differences between intervention and control groups in the relationship between PACT characteristics and each outcome at 6 months* 2) Differences among PACTs in frequency of referrals to weight loss and hepatology** 3) Barriers and facilitators to referral to weight loss and hepatology**
Implementation: *fidelity to elements of intervention*	1) Fidelity to MCCP intervention in terms of education/referral patterns and the relationship between degree of fidelity and each outcome at 6 months (based on documentation of checklist in CPRS)* 2) Adaptations of MCCP delivery by PACT members** 3) Time required to deliver MCCP as reported in interviews** 4) Patient experiences with PACT and providers using MCCP**
Maintenance: *extent to which intervention effects are sustained 6 or more months* (Examination of outcomes at 12 months)	1) Differences in the proportion of patients with MASLD who are NEWLY referred to weight loss program (within 6–12 months) between intervention and control groups* 2) Differences in the proportions of patients with advanced MASLD who are NEWLY referred to hepatology (6–12 months) between intervention and control groups* 3) Differences in the proportion of patients with MASLD who are referred to a weight loss program who actually start the program within 12 months between intervention and control groups 4) Differences in the proportion of patients with advanced MASLD referred to hepatology who actually see a hepatology clinic within 12 months between intervention and control groups

*quantitative measure

**qualitative measure

Qualitative data will include interviews with PCPs and nurses in both study groups to explore barriers and facilitators to the referral process and adaptations made while delivering the intervention (Table 3). Semi-directed content analysis will be used to analyze interview data [27]. This approach leverages pre-determined themes to structure analysis and allows new themes to emerge. RE-AIM framework will inform parent codes (e.g., adoption, implementation). Sub-codes (e.g., adoption: decision making) will allow for granular analysis and capture of various experiences.

**Table 3 Tab3:** PACT focus group questions for summative evaluation

Adoption

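### Table 2 and Outcomes compare referral and uptake between arms among patients diagnosed after randomisation, a group the intervention is designed to enlarge, and this conflicts with the unrestricted analysis plan

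*Protocol article*

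**What the plan says.** **Outcomes.** The primary outcome is defined thus: "The primary outcome will be a composite dichotomous variable of making a new MASLD diagnosis and completing severity risk stratification of MASLD". The next sentence turns to the secondary outcomes: "Secondary outcomes include referral and receipt of hepatology specialty care for patients with MASLD and advanced fibrosis".

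**Table 2, Effectiveness.** The contrasts are between arms and carry a disease restriction. For weight loss: "Differences in the proportions of patients with MASLD who are referred to a weight loss program within 6 months between intervention and control groups". For hepatology: "Differences in the proportions of patients with advanced MASLD who are referred to hepatology within 6 months between intervention and control groups". A further item concerns attendance: "Differences in the proportion of patients with advanced MASLD referred to hepatology and are seen in a hepatology clinic within 6 months".

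**Table 2, Maintenance.** One between-arm item counts "patients with advanced MASLD who are NEWLY referred to hepatology" in months 6 to 12. Another concerns "patients with advanced MASLD referred to hepatology who actually see a hepatology clinic within 12 months".

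**Sample size.** The trial is powered on 7% (usual care) against 17% (MCCP) detected and risk stratified, with about 8000 patients and 8 PACTs per arm.

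**Analysis plan for cluster-randomized trial, and Table 1.** Both list hepatology and weight-loss referral with no MASLD or advanced-fibrosis restriction, and Table 1 adds attendance and enrolment. The analysis plan specifies intention-to-treat and per-protocol multilevel models at 6 and 12 months, but does not state which patients form the denominator for these outcomes.

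**The concern.** Randomisation protects a comparison when the people compared are fixed before the intervention can act on them. Here, being known to have MASLD, and being staged as advanced, are results of the care under test. Usual-care PACTs receive neither the e-trigger lists nor the training, so case finding differs between arms by design. The Introduction says that most patients in practice are undetected, so the recorded group cannot stand in for true disease status. Fibroscan, one of the staging tools, is itself listed as an outcome in Table 1. The Discussion adds that the hepatology service requests MR elastography after a failed Fibroscan, so for some patients staging may depend on the very contact being counted.

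The 12-month uptake items go one step further and also condition on having been referred.

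The trial's hypothesis covers diagnosis, referral and treatment. The referral and uptake outcomes carry the second and third of these, so an ambiguous comparison would leave those claims hard to interpret.

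**Working it through.** **1. The plan's own figure.** No stated number is disputed, but the 7% and 17% are used below, so I checked that they drive the stated power. With m = 8000/8 = 1000 patients per PACT and two-sided alpha 0.05 (assumed, not stated):

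- ICC 0.04: design effect 1 + 999 × 0.04 = 40.96; effective n = 8000/40.96 = 195 per arm; power 86.3%.
- ICC 0.02: design effect 20.98; effective n = 381 per arm; power 99.0%.

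With a continuity correction these become 82.5% and 98.6%. The stated range of 84% to 99% is reproduced to within about 2 points.

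**2. Size of the post-randomisation groups.** Newly diagnosed and staged: 0.07 × 8000 = 560 in usual care, 0.17 × 8000 = 1360 under MCCP. Ratio 17/7 = 2.4. If the rates apply to only a subset of the 8000, the counts shrink and the ratio stays.

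**3. Two ways to compare referral.** Let r be the referral rate among patients whom usual care would detect (assumed unchanged under MCCP), and x the rate among the extra 10% whom only MCCP detects.

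- All patients: usual care 0.07r; MCCP 0.07r + 0.10x. The difference is 0.10x, positive for any x above 0.
- Among the diagnosed: usual care r; MCCP (0.07r + 0.10x)/0.17. The difference is 0.10(x − r)/0.17, negative whenever x is below r.

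**4. Illustration.** The article does not give r. As an assumption, take the chart review in the Introduction (10.4% referred to a specialist, 21.5% with MASLD mentioned) and suppose that all referred patients were among those recognised: r = 10.4/21.5 = 48.4%. Usual care then refers 271 of 560, which is 3.4% of 8000.

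| x (assumed) | MCCP referred of 1360 | Difference, all patients | Difference, diagnosed only |
|---|---|---|---|
| 10% | 351 | +1.0 points | −22.6 points |
| 20% | 431 | +2.0 | −16.7 |
| 30% | 511 | +3.0 | −10.8 |
| 40% | 591 | +4.0 | −4.9 |
| 50% | 671 | +5.0 | +1.0 |
| 60% | 751 | +6.0 | +6.8 |

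At x = 20%, referral over all patients rises from 3.4% to 5.4% (431/8000), while among the diagnosed it falls from 48.4% to 31.7% (431/1360). At x = r, the conditional difference is zero although referrals per patient rise 2.4-fold.

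**5. Sensitivity.** With r = 30% and x = 10%: +1.0 (all) against −11.8 (diagnosed). With r = 70% and x = 30%: +3.0 against −23.5. If MCCP also raises r by a factor of 1.25 in the patients usual care would have found, the conditional contrast changes sign near x = 0.825 × 48.4% = 40% instead of 48%.

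**6. New referrals in months 6 to 12.** Within a fixed denominator, new referrals equal the cumulative proportion at 12 months minus that at 6 months. The arm difference in new referrals is therefore the 12-month lead minus the 6-month lead. Assumed cumulative referral of 7% then 12% (usual care) and 17% then 20% (MCCP) gives new referrals of 5% and 3%, although MCCP leads by 20 − 12 = 8 points at 12 months.

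**The case against.** The strongest reply is that the trial's own analysis section lists the referral outcomes with no restriction, under intention-to-treat, and Table 1 collects them the same way. The sentence in Outcomes may simply name the kind of care, and Table 2 belongs to the summative evaluation. This stands in part: an all-patient analysis is an available reading. But the analysis section does not state that denominator, and Table 2 defines explicit between-arm contrasts with a different one. What remains is a conflict that must be resolved, not a settled commitment to the conditional version.

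A reader might also infer that the 6-month attendance item, "advanced MASLD referred to hepatology and are seen in a hepatology clinic within 6 months", is a proportion among referred patients. It can equally be read as a joint endpoint (referred and seen), as its weight-loss counterpart suggests. Only the 12-month uptake items clearly condition on referral.

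New referrals after month 6 are a legitimate measure of sustained activity, which is how Table 2 defines Maintenance. That stands: the measure needs the cumulative figure beside it, not removal.

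Finally, an article may leave analysis populations to a fuller document. Here, however, the article does state populations, and they disagree.

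**Conclusion.** The point holds as a conflict between sections and an exposure to selection bias in the referral and uptake contrasts. Followed as Outcomes and Table 2 word them, the denominators differ about 2.4-fold on the plan's own detection rates. That ratio describes newly diagnosed and staged patients; the article gives no corresponding rates for advanced disease, and counting patients already diagnosed at baseline would dilute it.

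A reader might infer that these comparisons will make an effective pathway look worse. The documents do not support that. A null or reversed result requires the extra MCCP-detected patients to be referred at the same or a lower rate than those usual care finds. This is plausible if case finding reaches milder disease, but the article gives no such rates, and MCCP also trains teams on referral, which could push the other way. All referral rates in the illustration are assumptions.

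The primary outcome, Fibroscan testing and documentation of MASLD discussion carry no such restriction and are unaffected.

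**What to change.** Reconcile Outcomes, the trial analysis plan and Table 2 on one rule for between-arm comparisons:

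- Use a denominator fixed at the index date and identified identically in both arms: either all enrolled patients, or e-trigger-positive patients computed from records in both arms. Use only values dated before the index date.
- If an advanced-risk subgroup is wanted, define it by a prespecified threshold on pre-index FIB-4. The pathway figure is not shown here, so I name no value.
- Score referred and seen as yes/no for every patient in that denominator.
- Report proportions among the diagnosed, staged or referred as descriptive only.
- For Maintenance, make the cumulative proportion by 12 months the between-arm comparison, and keep new referrals in months 6 to 12 as a supplementary description.

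The cost is a change of wording: Table 1 already draws referral, attendance and enrolment from the corporate data warehouse at 6 and 12 months. The downside is smaller absolute percentages, such as 3.4% against 5.4% in the illustration above.
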